### **8.2 STATISTICAL PROCEDURES**

All statistical analysis described in this protocol will be performed by the investigator. All analysis and tabulations will be performed using the latest release of the SAS® or SPSS software or similar statistical software. Appropriate descriptive statistics will be presented for each variable; n=number of patients, mean, median, SD and min-max for continuously distributed variables, and rates and percentages for categorical variables. Statistical tests will be performed using 5% as the nominal level of significance and interval estimates will be constructed using 95% as the level of confidence. Statistical and analytical methods, and sample size considerations are discussed in the following sections. The investigator will make the decisions regarding subjects, or individual values belonging to a patient, to be excluded from the analysis. Subjects will only be excluded from the efficacy analysis when the uses of these are considered a protocol violation, putting the scientific aspects of the trial at risk. The variables that will be statistically tested are given in the Sections concerning primary and secondary variables.

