### 8.2.2 MAIN OUTCOME MEASURES

The main outcome measures in this study for adults are body weight loss maintained (kg), changes in body composition (DEXA/bioimpedance), proportion of subjects maintaining > 0, 5 and 10% of initial weight loss, and drop-out rate. Main outcome measures for children are changes in the proportion of overweight and obese children at 6 and 12 mo, and changes in age-associated BMI, % whole body fat and drop-out rate.

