### 8.2.4 STATISTICAL METHODS FOR THE PRIMARY OBJECTIVES

Analysis of Covariance (ANACOVA) will be used to compare the main outcome measures in the intervention groups at week 26 and week 52 using the data from CID2 (after weight-loss, adults) or CID1 (children) as covariate.

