### 8.2.5 PRIMARY HYPOTHESIS

The following primary hypothesis can be applied:

H0: The 1o outcome (weight, etc) is equal in the intervention groups at week 26 and week 52, when controlling for the value in CID2 (adults) or CID1 (children).

vs.

H1: The 1o outcome is different in the intervention groups at week 26 and week 52, when controlling for the value in CID2 (adults) or CID1 (children).

The changes in continuously distributed variables from baseline to week 26 and week 52 within treatment groups will be tested with the paired t-test or the Wilcoxon-Signed-rank test, depending on distribution (all tests two-sided).

All categorical variables will be expressed in contingency tables and analyzed using Fisher's exact test. Survival analysis using the Kaplan-Meier plot and the log-rank test will be used to investigate time to subject withdrawal.

All null hypotheses comparing groups assume equality between the treatment groups while the alternative hypotheses assume that there is a difference (two-sided). All within-group null hypotheses assume no change from baseline to week 26 or week 52 while the alternative hypotheses assume that there is a change (two-sided).

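### Section 8.2.5 names no paired test for within-group change in overweight/obese status; read literally, it puts Fisher's exact test on the same children's repeated measurements

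*Protocol*

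**What the plan says.** Protocol section 8.2.2 lists the outcome without restricting it to children who are overweight at entry: "Main outcome measures for children are changes in the proportion of overweight and obese children at 6 and 12 mo". Section 7.1.2 has all children weighed and their height measured at CID1, week 26 and week 52, so status is a repeated yes/no observation on each child.

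Section 8.2.5 then sets four rules:

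- Within treatment groups, changes in continuous variables "will be tested with the paired t-test or the Wilcoxon-Signed-rank test, depending on distribution (all tests two-sided").
- For categorical data: "All categorical variables will be expressed in contingency tables and analyzed using Fisher's exact test".
- Between groups: "All null hypotheses comparing groups assume equality between the treatment groups".
- Within groups: "All within-group null hypotheses assume no change from baseline to week 26 or week 52 while the alternative hypotheses assume that there is a change".

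The fourth rule is not limited to continuous variables, and no paired categorical test is named anywhere. Section 8.2 sets the level: "Statistical tests will be performed using 5% as the nominal level of significance".

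The primary inference lies elsewhere. Section 8.2.4 says "Analysis of Covariance (ANACOVA) will be used to compare the main outcome measures in the intervention groups at week 26 and week 52", and the primary hypothesis in 8.2.5 compares groups "when controlling for the value in CID2 (adults) or CID1 (children").

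**The concern.** Fisher's exact test assumes that the two rows of the table are independent samples. In a visit-by-status table each child appears once per row, so the child is counted twice and the information in the pairing is lost. The authors respected pairing for continuous variables in the same section, so its absence for categorical variables looks like an oversight.

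At stake is the within-arm p-value for one of the children's main outcomes. If the literal rule were followed, a real fall or rise in the proportion overweight on a given diet could be reported as non-significant when a paired test on the same children would detect it.

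**Working it through.** **Plan's own figure.** There is none to reproduce. Section 8.2.7 gives a sample size only for weight change to week 26. Child proportions, correlations and effect sizes below are therefore assumptions.

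**Inputs on numbers.** The Synopsis gives 350 families in the whole project, and there are five arms: 350/5 = 70 families, so 70 children per arm at one child each. Section 4.2 gives about 11 families per arm locally, so about 22 children at two each (section 5.1 allows 1–3).

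**Why pairing matters.** Let p1 and p2 be the proportions at the two visits and φ the within-child correlation of status.

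- Per-child variance of the change if visits are independent: p1(1−p1) + p2(1−p2).
- Per-child variance with pairing: the same, minus 2φ√[p1(1−p1)·p2(1−p2)].

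For 70% falling to 60% with φ = 0.7: independent, 0.21 + 0.24 = 0.45; paired, 0.45 − 2(0.7)√(0.21 × 0.24) = 0.45 − 0.314 = 0.136. The unpaired test works with a variance about 3.3 times too large (0.45/0.136).

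**Worked tables.** Exact McNemar uses only the b children who improve and the c who worsen: p = 2·Σ C(b+c, k)/2^(b+c), summed over k from 0 to min(b, c).

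| Overweight, before → after | Improve / worsen | Fisher p | Exact McNemar p |
|---|---|---|---|
| 49/70 → 40/70 | 10 / 1 | 0.16 | 2(1+11)/2048 = 0.012 |
| 15/22 → 9/22 | 6 / 0 | 0.13 | 2/64 = 0.031 |
| 70/70 → 64/70 | 6 / 0 | 0.028 | 2/64 = 0.031 |
| 11/11 → 6/11 | 5 / 0 | 0.035 | 2/32 = 0.063 |

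The first two rows show the conservatism. In the last two, where every child is overweight at baseline, it has gone or reversed.

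**Rejection rates with φ set directly** (simulated paired binary data, 20,000 draws, two-sided 5%):

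| Children | Change | φ | Fisher | Exact McNemar |
|---|---|---|---|---|
| 70 | 70% → 70% | 0 | 3.1% | 2.8% |
| 70 | 70% → 70% | 0.5 | 0.3% | 2.9% |
| 70 | 70% → 70% | 0.7 | about 0% | 2.3% |
| 70 | 70% → 60% | 0 | 18.5% | 17.5% |
| 70 | 70% → 60% | 0.5 | 10% | 33% |
| 70 | 70% → 60% | 0.7 | 6% | 49% |
| 140 | 70% → 60% | 0.7 | 27% | 87% |
| 22 | 70% → 55% | 0.7 | 2% | 10% |

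**Rejection rates from an underlying BMI scale.** Baseline is x ~ N(0,1), follow-up is y = ρx + √(1−ρ²)·e − shift, and a child is overweight above −0.5. That puts 69% above the cut at baseline, and a shift of 0.4 SD lowers it to 54%. With ρ of 0.8–0.9:

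- No shift: Fisher rejects in 0–0.3% of trials.
- Shift 0.4, 70 children: Fisher 30–34%, exact McNemar 72–84%.
- Shift 0.4, 22 children: Fisher about 2–4%, exact McNemar about 11–13%.

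All these simulations treat children as independent and ignore sibling clustering.

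**The case against.** The strongest reply is that the protocol never says Fisher's test will compare two visits. The sentence naming it mentions no visit-by-status table, and the hypotheses around it compare diets. A diet-by-status table is a natural reading, and an unpaired test is legitimate there. This stands in part: on that reading the within-group categorical test is unspecified rather than wrong, and such detail could sit in an analysis plan. But the protocol is not silent. It assigns one test to all categorical variables and applies within-group nulls without exception, so the literal reading remains open and the same edit closes both.

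Second, the within-group tests are supporting. Diets are judged against each other and against control, and age-associated BMI, also a main child outcome, already has a paired within-group test. This stands and limits the weight of the point. It also means the documents give no reason to ask that the child conclusion rest on BMI instead; that would be a preference.

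Third, a reader might infer that real change is bound to be missed. The documents do not support that. They give no correlation or baseline prevalence; at φ = 0 the two tests perform alike, and with all children overweight at baseline Fisher is no longer the more conservative. Section 8.2.2 does not restrict the outcome to overweight children, so prevalence below 100% is the more natural reading, but it is not stated.

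Fourth, at about 22 children per arm McNemar has little power too, so the change of test does not rescue the outcome at local size. That stands. Under positive correlation with prevalence below 100%, the error is also towards too few rejections, not false positive claims.

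**Conclusion.** The point holds as a defect of wording with a conditional statistical cost. Followed literally, section 8.2.5 applies an unpaired test to paired data for the within-group change in a main child outcome. Given positive within-child correlation and baseline prevalence below 100%, that test is too conservative; at project size (70 per arm) and under the assumed BMI model, it has less than half the power of exact McNemar. The size rests wholly on assumed correlations, prevalence and shift, and on treating children as independent. It should not be read as showing that the p-values will be wrong, since the text does not expressly run Fisher across visits, nor as touching the primary between-group comparison.

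**What to change.** In section 8.2.5:

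1. Limit Fisher's exact test to unpaired tables comparing treatment groups.
2. Test within-group change in overweight/obese status from CID1 to week 26 and to week 52 with exact McNemar, or with a marginal-homogeneity test if normal, overweight and obese are kept as three categories.
3. Report the change in proportion with a paired 95% CI.
4. Because families contribute 1–3 children and McNemar treats siblings as independent, allow as an alternative a logistic GEE model with a visit term, clustered on family. With only about 11 families per arm locally, its standard errors would need a small-sample correction.

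The cost is two or three sentences, with no extra data, visits or participants.

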### **8.2.6 STATISTICAL METHODS FOR SECONDARY OBJECTIVES**

ANCOVA will be used to compare the secondary variables at week 26 between treatment groups using the relevant data from CID2 (after weight-loss, adults) or CID1 (children) as covariate.

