### Dietary periods

- 1) Adult subjects only: 8 week Low Calorie Diet (LCD) period (liquid formula diet, 800-1000 kcal/day).
- 2) 6 months dietary intervention period 1 (SUPERMARKET period) followed by
- 3) 6 months dietary intervention period 2 (DIETARY INSTRUCTION period).
- 4) 12 months free-living period with no dietary intervention.

[figure not shown]

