#### 1. 8 week LCD dietary period

The energy restricted LCD diet (for adults only) will consist of 800-1000 kcal/d and the target macronutrient composition of the diet will be 15-20% of total energy from fat, 35-40% from protein and 45-50% from carbohydrate. No energy restriction will be imposed for the children in the enrolled families. During this period, subjects will attend approx. 6 group meetings at the Department where their body weight, adverse events (AE) and concomitant medication will be registered and dietary and behavioural instructions will be given.

Before entering intervention period 1, adult subjects visit the Department for CID 2. This will again include anthropometric measurements, BP, blood sample and 24-h urine collection, fat biopsy, OGTT, analysis of body composition (DEXA scan), and completion of lifestyle/behavioural questionnaires. Families where at least one parent achieves a  $>8\%$  weight loss will be randomised to one of the 5 dietary arms.

Subgroup a will complete a 7-day food record and undergo BMR and DLW measurements, have physical activity measured by use of a pedometer and have a meal test.

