### **7.3.2 BLOOD LIPID PROFILE**

Blood lipids are determined on CID 1-4 for adults only.

Measurements of fasting total HDL, total LDL, VLDL cholesterol, total cholesterol and triglycerides are performed.

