### **7.3.4 GLUCOSE SENSITIVITY**

An OGTT will be performed on adult subjects on CID 1-4. Each subject will take a load of 75 g glucose within a 5 min period. The subjects will remain semi-recumbent and resting throughout the procedure, and must fast (except for 1 dL of water) until completion of the test. Blood samples will be obtained for glucose and insulin at 0, 30, 60, 90 and 120 minutes after drinking the liquid glucose solution. The 0 and 60 min samples will also be analyzed for small and large-sized peptides (i.e. peptidomic/proteomic analyses).

Information about the OGTT-procedure will be given out to the subject. During the OGTT subjective appetite ratings will be made using Visual Analogue Scales (VAS).

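### Adult secondary outcomes are adjusted only for the end-of-LCD value although CID 1 is also collected, so precision may be lost; and within-arm tests from an unnamed baseline do not isolate the assigned diet

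*Protocol*

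**What the plan says.** On the between-arm analysis, section 8.2.6 states that "ANCOVA will be used to compare the secondary variables at week 26 between treatment groups". The rest of that sentence fixes the adjustment, and for adults it names a single visit: "using the relevant data from CID2 (after weight-loss, adults) or CID1 (children) as covariate".

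On the timing of CID 2, Section 3 (8 week LCD dietary period) says "The energy restricted LCD diet (for adults only) will consist of 800-1000 kcal/d" and then "Before entering intervention period 1, adult subjects visit the Department for CID 2". Section 7.1.1.7 places the visit in week 0. No stabilisation interval between the LCD and CID 2 is described.

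On what else is available, Section 3 puts CID 1 in the three weeks before the LCD. Section 7.3.2 says "Blood lipids are determined on CID 1-4 for adults only" and section 7.3.4 says "An OGTT will be performed on adult subjects on CID 1-4". Sections 7.3.1, 7.3.3 and 7.3.5 give the same visits for waist, hip and sagittal measurements, for coagulation factors, inflammatory markers and appetite hormones, and for blood pressure. No adult analysis in section 8.2 names the CID 1 value.

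On within-arm change, section 8.2.5 says that changes in continuous variables from baseline to weeks 26 and 52 "within treatment groups will be tested with the paired t-test or the Wilcoxon-Signed-rank test". It adds two-sided within-group null hypotheses of no change. It does not say which visit is the baseline.

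**The concern.** Adult CID 2 is taken at the end of energy restriction, whereas the week-26 value follows six months of ad libitum eating. For a marker that responds to current energy intake, or one that varies a good deal within a person, a single end-of-LCD reading may be a weak predictor of week 26. A second pre-intervention reading, already paid for, may then explain variance that CID 2 leaves unexplained. This matters somewhat more because section 8.2.7 states that nothing except 26-week weight change has a sample size calculation.

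The within-arm tests raise a question of interpretation. A significant change in, say, lipids or insulin within one arm could be reported as an effect of that diet on cardiovascular or diabetes risk, when part or all of it reflects the LCD or its ending.

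**Working it through.** **1. Precision of the between-arm contrast**

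The plan gives no precision or power figure for the secondary outcomes, so there is none to reproduce. It also gives no correlations between visits; those below are assumptions.

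Notation: r2 = correlation of CID 2 with week 26; r1 = correlation of CID 1 with week 26; r12 = correlation of CID 1 with CID 2.

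- CID 2 alone: R² = r2².
- CID 1 and CID 2: R² = (r1² + r2² − 2·r1·r2·r12) / (1 − r12²).
- Residual variance ratio = (1 − R² with both) / (1 − R² with CID 2 alone).

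Worked case, r2 = 0.5, r1 = 0.7, r12 = 0.6: R² = (0.49 + 0.25 − 0.42) / 0.64 = 0.50, against 0.25 for CID 2 alone. The ratio is 0.50 / 0.75 = 0.67.

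| r2 | r1 | r12 | R², CID 2 | R², both | Ratio |
|---|---|---|---|---|---|
| 0.5 | 0.3 | 0.6 | 0.25 | 0.250 | 1.00 |
| 0.7 | 0.5 | 0.7 | 0.49 | 0.490 | 1.00 |
| 0.6 | 0.4 | 0.6 | 0.36 | 0.363 | 0.996 |
| 0.5 | 0.4 | 0.6 | 0.25 | 0.266 | 0.98 |
| 0.8 | 0.7 | 0.8 | 0.64 | 0.650 | 0.97 |
| 0.5 | 0.5 | 0.6 | 0.25 | 0.312 | 0.92 |
| 0.6 | 0.6 | 0.6 | 0.36 | 0.450 | 0.86 |
| 0.7 | 0.7 | 0.7 | 0.49 | 0.576 | 0.83 |
| 0.5 | 0.6 | 0.6 | 0.25 | 0.391 | 0.81 |
| 0.5 | 0.7 | 0.6 | 0.25 | 0.500 | 0.67 |
| 0.4 | 0.7 | 0.5 | 0.16 | 0.493 | 0.60 |

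The gain is nil when r1 = r2 × r12, that is, when CID 1 tells us nothing about week 26 beyond what CID 2 tells us (first row: 0.5 × 0.6 = 0.3). It is moderate when the two visits act as repeat readings of the same quantity (rows with all three correlations equal: 14% to 17%). It is largest when CID 1 predicts week 26 better than CID 2 does. A ratio of 0.60 (0.603 before rounding) equals about 1/0.603 − 1 = 66% more subjects. The upper end is set by the cases chosen, not by the documents.

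Cost of the extra covariate: with five arms, the model goes from six to seven parameters, and the variance rises by about (N − 6 − 2) / (N − 7 − 2). The Synopsis gives 110 adults for randomisation and more than 80 completing 12 months. N = 80: 72/71 = 1.014. N = 110: 102/101 = 1.010. The cost is about 1%.

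**2. Within-arm change**

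The protocol points two ways on the baseline visit:

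- Section 7.1.1.2 describes Visit 2 (CID 1) as the baseline examination.
- Section 8.2.7 says that the covariate method controls for the baseline value, and for adults the covariate in 8.2.4 to 8.2.6 is CID 2.

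Take each in turn for an adult in arm k:

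- From CID 2: expected change = (effect of ending energy restriction) + (effect of diet k).
- From CID 1: expected change = (effect of the LCD weight loss still present) + (effect of diet k).

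A paired test in one arm sees only the sum, so it cannot separate the two terms on either reading. Every arm goes through the same LCD, so in the difference between arms the shared term drops out. That is the contrast 8.2.6 already specifies.

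**The case against.** The strongest reply is that ANCOVA on the value at the start of the randomised diets is standard and valid, suits a question about maintaining weight loss, and is used consistently for adults in 8.2.4, 8.2.5 and 8.2.6. A second covariate is then a refinement that an analysis plan, not shown here, could add. The validity and consistency stand. But 8.2.6 does fix the covariate, and the omitted value is collected at no extra burden.

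Four stronger readings are tempting, and the documents do not support them.

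- A reader might infer that the diet comparison is biased. It is not: all arms share the LCD, and adult CID 2 precedes intervention period 1. The visit follows the randomisation meeting in week 0, but nothing shows that allocation could alter its values.
- A reader might infer that precision is certainly lost. Without correlations this cannot be shown, and the gain can be zero. Nor can it be turned into a power figure, because the protocol has no planning assumptions for these outcomes.
- A reader might infer that CID 1 is closer to the week-26 state for every outcome and should replace CID 2. For weight-driven variables such as waist the reverse may hold: at least one parent per family must lose more than 8% on the LCD, and the intervention aims to keep that loss.
- A reader might infer that every within-arm test is contaminated by refeeding, or that the plan intends to claim diet effects from those tests. The first depends on CID 2 being the baseline, which is not stated. As to the second, sections 4.2 and 8.2.1 frame the objective as comparison between diets and with control.

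What survives is that 8.2.5 gives the within-arm tests formal null hypotheses, and that they do not isolate diet on either reading.

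**Conclusion.** The point holds as one of efficiency and interpretation; it does not invalidate the analysis. For adult secondary outcomes the randomised contrast is unbiased, but its precision may be below what the collected data allow, mainly for markers sensitive to current energy intake or with high within-person variation. Over the assumed correlations, the reduction in residual variance from adding CID 1 runs from 0% to about 40%, against a cost of about 1%. Where the gain falls in that range will differ by outcome.

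The within-arm part needs no correlations. It rests on the wording of 8.2.5, which names no visit, and on the order of the LCD and the visits. Whichever visit is meant, the test mixes the LCD or its ending with the assigned diet.

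**What to change.** - **Section 8.2.6:** keep the CID 2 value and add the CID 1 value as a second covariate for adult secondary variables measured at both visits.
- **Section 8.2.5:** name the baseline visit. Report within-arm changes from CID 2 and from CID 1 side by side as descriptive only, noting what each includes. State that conclusions about diet rest on the between-arm contrasts.

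The cost is one degree of freedom per model, simple covariate imputation for adults without a CID 1 value, and one more column in the tables. Some outcomes may gain nothing. No visit, measurement or clinical procedure changes.

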### **8.2.7 SAMPLE SIZE ESTIMATION**

The primary aim of the study is to investigate the long-term efficacy in terms of change in body weight from baseline to study end. The sample size for the proposed study was chosen to provide sufficient power to detect differences in 26-week weight regain (for primary participants) due to the effects of the different diets. The sample estimation is based on the difference between the intervention and control groups regarding weight change (kg) from baseline to week 26. In the null hypothesis we assume that the interventions groups 1 - 4 are of equal weight at week 26 compared to baseline, while the alternative hypothesis assumes that there exists a difference in weight between the treatment groups. By this covariate method we are able to test the change from baseline to week 26 while controlling for between-group differences in the baseline value.

It is anticipated that weight differences will be smallest between the low vs. high GI diets compared to the low protein vs. high protein diets. Hence the sample size has been calculated on the basis of a previous intervention study on GI (18), which found a non-significant difference in body weight change of 0.6 kg between groups using the unpaired t-test. We assume a 0.4 kg higher weight loss based on 6-month treatment, compared to the 10-week previous intervention study (18). Thus we consider that a weight loss difference of 1 kg is a clinically relevant weight loss and a priori we assume a SD of 2.01 kg.

When assuming a difference between control and intervention group of 1.0 kg (SD 2.5 kg), at least 80% statistical power and a significance level of 5%, N=125 participants per group are required (unpaired t-test). In this model, any effect size above 0.72 kg gives a power of more than 80%.

As most other studied variables in the study are secondary objectives and because the outcome of most of these variables are not easily comparable to previous studies due to the novel design of the study, there are no calculations on sample size for variables other than the primary efficacy parameter, which is weight change to week 26.

Thus, in terms of final outcome, it is accepted that post-hoc analysis will identify that not all measures of other primary or secondary outcomes will necessarily have had the appropriate sample size.

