## Aims

The main objective of the DiOGenes study is to identify the efficacy of particular diets for protection against weight gain and weight regain, in a susceptible population of obese and overweight individuals and their children. The overall study comprises a 6 to 12 months dietary intervention study in 350 families in 8 European countries (Denmark, the Netherlands, UK, Germany, Spain, Greece, Bulgaria and the Czech Republic), investigating the effect of different dietary components (high/normal protein and high/low GI) on maintenance of weight loss and prevention of weight (re)gain. In Denmark/Netherlands the study will be carried out over 12 months, in about 50 families. The responsiveness of the families to different dietary compositions and effects on body weight control and obesity related risk factors will be assessed during the dietary intervention study, with specific focus on changes in body weight and composition, appetite measures, adipose tissue gene expression and risk factors for cardiovascular disease (CVD) and type-2 diabetes. The role of genetic, environmental, social and cultural factors as well as their interactions with the studied diets on body weight control or development of obesity will also be investigated.

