## Subjects

Families where both parents are < 65 years old, and where at least one parent is obese (BMI>30 kg/m^2) and the other is overweight (BMI>28 kg/m^2) will be offered inclusion in the study with the aim of losing weight and maintaining the weight loss. Families will have 1-3 children, and at least one child aged between 5 and 18 years will be overweight (defined according to Cole *et al.* (2), i.e. with an iso-BMI>25). A total of 150 adult subjects plus children (75 families) will be screened and approximately 135 adults are expected to be included in the initial weight loss phase of the study, with the aim of having a total of 110 subjects for the subsequent randomization to the 5 dietary

arms. This number will provide an anticipated completion of more than 80 subjects at the 12-month visit.

Subjects will be recruited through the department's waiting list, local press or via referrals from local general practices or from other medical departments. Radio/television or newspaper advertising may also be employed if necessary. Eligible subjects will only be included after they have been informed about the study and signed informed consent forms (including children, see Section 11).

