## 4.2 METHOD OF ASSIGNING FAMILIES TO DIETARY GROUPS

The eligible families will be allocated to a dietary intervention group using a simple block randomization procedure with centre, number of obese parents in the family and BMI (greater or less than 34, screening value) as stratification criteria by a third party with no knowledge of the

subjects that may affect the outcome of the study. Approx. 11 families are randomized to each of the 5 dietary intervention groups. The outcome in the dietary intervention groups will be compared to each other and to the control group.

Approx. 6 subjects in each dietary group (3 men and 3 women) will be randomized to **Subgroup a** (7-day food record, BMR and DLW measurements, physical activity using pedometers, meal test). Approx. 7-10 subjects in each dietary group will be randomized to **Subgroup b** (extra fat biopsy day 3 into LCD diet).

Participation by (adult) subjects in the sub-groups is entirely voluntary and separate information sheets and consent forms will be signed.

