#### Handling of missing values

Since the sample size estimations take into account the drop-outs during the study, sufficient data should be obtained.

The primary analysis of data will be an "intention to treat" analysis (with only actual values presented) and will include only subjects having completed the study. We will also perform sensitivity analyses by examining different models of missing data and describe the range of possible outcomes based on the various models. For example, we will perform a "baseline carried forward" analysis and a "last observation carried forward" analysis as part of the sensitivity analysis.

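### The sample-size paragraph mixes two SDs: its 0.72 kg detectable difference does not follow from its own SD of 2.5 kg, and it does not say what drop-out or which population its 125 per group assumes

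*Protocol*

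**What the plan says.** Section 8.2.7 gives the only power calculation, for weight change to week 26. It takes 1 kg as the relevant difference and says "a priori we assume a SD of 2.01 kg". The next paragraph starts from another SD, "a difference between control and intervention group of 1.0 kg (SD 2.5 kg", with at least 80% power and a 5% level, and concludes "N=125 participants per group are required (unpaired t-test). In this model, any effect size above 0.72 kg gives a power of more than 80"%. Section 8.2.5 makes the tests two-sided.

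Section 8.2.4, on missing values, says "Since the sample size estimations take into account the drop-outs during the study, sufficient data should be obtained". It gives no rate and restricts the primary analysis to subjects who complete.

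On numbers, the Synopsis (Aims) describes 350 families in eight countries. Of the longer follow-up it says "In Denmark/Netherlands the study will be carried out over 12 months, in about 50 families". The Synopsis (Subjects) plans recruitment "with the aim of having a total of 110 subjects for the subsequent randomization to the 5 dietary" arms and expects more than 80 adults to complete 12 months. Section 4.2 says "Approx. 11 families are randomized to each of the 5 dietary intervention groups".

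**The concern.** The detectable-difference sentence is tied to the model of the sentence before it, so 125 and 0.72 kg should both follow from SD 2.5 kg. Neither does. There are also three unknowns: which SD the sponsor believes, whether 125 counts adults randomised or adults evaluable, and whether it describes the whole project or the adults recruited under this protocol.

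This is the only statement of what the trial can detect on its primary efficacy variable. A reader would take it that a 0.72 kg difference between diets is detected four times in five. At the SD in the same paragraph, the chance is nearer one in two or three in five.

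**Working it through.** **Inputs.** Difference 1.0 kg; SD 2.5 kg or 2.01 kg; power 80%; unpaired t-test; 125 per group; 0.72 kg (all section 8.2.7). Two-sided 5% (sections 8.2 and 8.2.5). 110 adults in five arms, more than 80 completing (Synopsis, Subjects). 350 families (Synopsis, Aims).

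**Formulas.** Normal approximation: n per group = 2·SD²·(1.960 + 0.842)²/difference², and detectable difference = 2.802·SD·√(2/n). Exact results use the noncentral t distribution with noncentrality difference/(SD·√(2/n)) and 2n − 2 degrees of freedom.

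**Step 1: the stated N.**
- SD 2.5: 2 × 6.25 × 7.851/1.0² = 98.1, so 99; the exact t-test gives 99.1, so 100 per group.
- SD 2.01: 2 × 4.040 × 7.851 = 63.4, so 64; the exact t-test gives 64.4, so 65 per group.
- Neither gives 125. At 125 evaluable, exact power for 1.0 kg is 88% (SD 2.5) or 97% (SD 2.01).
- 100/(1 − 0.20) = 125, so a 20% drop-out allowance would reproduce the figure. The protocol states no such rate.

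**Step 2: the stated 0.72 kg.**
- SD 2.5, n = 125: 2.802 × 2.5 × √(2/125) = 0.886; exact 0.889 kg.
- SD 2.01, n = 125: 2.802 × 2.01 × √(2/125) = 0.712; exact 0.715 kg. This reproduces the plan's figure.

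| SD (kg) | Evaluable per group | Power at 1.0 kg | Power at 0.72 kg | Detectable at 80% power |
|---|---|---|---|---|
| 2.5 | 100 | 80% | 53% | 1.00 kg |
| 2.5 | 125 | 88% | 62% | 0.89 kg |
| 2.01 | 100 | 94% | 71% | 0.80 kg |
| 2.01 | 125 | 97% | 81% | 0.72 kg |

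At SD 2.5 kg, 80% power for 0.72 kg would need 191 evaluable per group.

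**Step 3: can one set of inputs give both figures?** The 125 fits SD 2.5 with 20% drop-out; the 0.72 kg fits SD 2.01 with none. If 125 already includes drop-out, 100 remain and 0.72 kg misses 80% power under either SD. One-sided tests, stricter significance levels, 85% and 90% power, unequal or pooled arms and other drop-out adjustments were also tried. No single set produced both figures.

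**Step 4: which population.** Five arms of 125 make 625 adults. The local plan is 110/5 = 22 per arm, which matches about 11 families with two adults each. The whole project gives at most 350 × 2/5 = 140 per arm, fewer with single-parent families. Only the pooled trial can reach 125.

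For the local and 12-month comparisons at SD 2.5 kg, the exact detectable difference is 2.16 kg at 22 per arm. If the 110 adults are only one of the two 12-month centres' share, pooling both gives about 44 per arm and 1.51 kg. Both are as randomised, before losses.

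**The case against.** **The 125 is on the safe side.** The protocol asks for at least 80% power, and 125 evaluable gives 88%. Section 8.2.4 says drop-out is built in, and 100/0.8 is exactly 125. This stands: a reader might infer that the trial is too small for its 1.0 kg target, but the figure does not show that. What is missing is the rate.

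**The contrast with 22 per arm may not be like with like.** A reader might infer that the trial has about 25% power, the value for 1.0 kg at 22 per arm and SD 2.5 kg. The document points the other way. It describes an eight-country study, stratifies by centre and sets up a central data hub, and section 3 labels the roughly 50 families as Denmark's. The 125 is most likely the pooled target and the 22 a local share. What remains is that section 8.2 never says so.

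**Week 52 is partly disclosed.** Section 8.2.7 confines the calculation to week 26 and accepts that other outcomes may lack a suitable sample size. Section 8.2.5 nevertheless puts week 52 in the primary hypothesis, so a plain statement that it is not powered would help.

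**A null result will be read from its confidence interval.** Section 8.2 plans 95% intervals, and these, not the planning figure, show what is excluded. That limits the harm but does not make the stated power right.

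None of this rescues 0.72 kg within a model whose SD is 2.5 kg.

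**Conclusion.** The concern holds for the internal arithmetic. Section 8.2.7 uses two SDs in one calculation. Under its stated model the detectable difference at 125 evaluable is 0.89 kg, not 0.72 kg, and power at 0.72 kg is 62%, or 53% if 125 includes 20% drop-out. The 0.72 kg figure is valid only for SD 2.01 kg with 125 evaluable.

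The document does not support a claim that the week-26 comparison is under-powered for 1.0 kg. At SD 2.5 kg, power is 80% with 100 evaluable and 88% with 125, if the pooled trial delivers those numbers.

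These results treat adults as independent and use the planned unpaired t-test at a two-sided 5% level for one comparison. Families are randomised, so two adults in a household may respond alike. The documents give no intra-family correlation. Assuming 0.1 to 0.3, with two adults per family, 100 adults carry the information of 100/1.1 = 91 to 100/1.3 = 77, and power for 1.0 kg falls to about 77% to 69%. The 20% drop-out is likewise only an inference. The Synopsis implies up to 1 − 80/110 = 27% loss by 12 months; if that applied at week 26, 125 would leave about 91 adults and 77% power.

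**What to change.** Rewrite section 8.2.7 as follows.

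- Choose one SD and say where it comes from.
- State the sponsor's own drop-out rate, and give both the number randomised and the number evaluable per group.
- Give the matching detectable difference: for SD 2.5 kg, 1.00 kg at 100 evaluable or 0.89 kg at 125; for SD 2.01 kg, 0.80 kg or 0.72 kg. Delete 0.72 kg unless SD 2.01 kg with 125 evaluable is meant.
- State that N and power refer to the pooled eight-centre comparison at week 26.
- State that this calculation does not power the week-52 and local comparisons. At SD 2.5 kg their detectable difference is about 2.2 kg at 22 per arm or 1.5 kg at 44, depending on whether the 110 adults come from both 12-month centres or one.
- Note that the figures ignore clustering of adults within families, or add a design effect with its assumed correlation.

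The cost is one rewritten paragraph. Arms, endpoint, test and participant numbers stay as they are; the stated figures become slightly less favourable.
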